### (Planned) statistical analyses

All statistical analyses will be performed using Stata 13.1 (www.stata.com). For each questionnaire separately, (missing) data will be managed according to recommendations of the specific questionnaire. Descriptive statistics will be used to present group characteristics. Normality will be assessed for continuous data by checking histograms. Continuous variables will be reported as mean and SD or median and inter-quartile ranges, as appropriate. For nominal variables, number (N) and percentage (%) will be presented. The primary analysis will be performed according to the intention-to-treat principle. In addition, a per-protocol analysis, including adherent participants of the dr. Bart group and the entire usual care group will serve as sensitivity analyses. In order to check for selective attrition, baseline characteristics of completers and non-completers of the study will be compared. In all analyses, a two-tailed significance level of *p* < 0.05 is regarded as statistically significant. Differences between treatment arms at baseline will not be statistically tested.

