#### Randomization, allocation concealment and blinding

Dutch consenting participants will be randomly allocated by the researcher to usual care (A) or dr. Bart (B) (allocation ratio 1:1) after completing baseline assessment performed with CastorEDC. CastorEDC uses a validated variable block randomization method (with randomly varying block sizes of 2, 4 and 6) and is stratified on the individual level by hip or knee OA. The researcher who will ascertain randomization will be concealed for treatment allocation. Due to the design of this study, blinding of participants and researchers is not possible. Data collectors will be blinded as data will be collected with validated questionnaires via CastorEDC. All German participants receive the dr. Bart app during the study (C), see Fig. 2.

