#### Adherence to the dr. Bart app

Adherence to the dr. Bart app will be quantitatively measured in the back end of the app. Parameters of use will be logged and extracted automatically for each user:
*The proportion of active users (*e.g. *who completed minimal one goal) over time*
*Number of average logins per active user per week*

*Number of recommended goals, not chosen*

*Number of chosen goals*

*Number of achieved goals*
*Number of goals set to non-active (*i.e. *choose to not do goal anymore)**Number of goals set to active (*i.e. *choose to do goal again)*
*Ranking of goals on the basis of times chosen*

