### Sample size

The primary outcome measure for the RCT is number of consultations in secondary health care due to OA of the knee and/or hip in the past 6 months. We performed a sample size calculation for an unpaired t-test to compare two independent means. Based on previous research a mean difference of 0.35 consultations between two independent groups was considered credible, with a standard deviation (SD) of 1.00 [68]. With a power of 0.80 and an alpha (α) of 0.05 (two-sided) a sample size of 129 participants per arm is needed. Accounting for loss to follow-up of 20%, 161 participants per arm will be included. Sample size was calculated with Stata version 13.1.

The second aim of the presented study is to explore cultural differences in use and usability of the app and its effect on clinical outcomes. For pragmatic reasons, we decided to include 161 participants (including 20% loss to follow-up) as well in the German arm of the study (C). A total of 129 participants is sufficient to detect a minimal difference of 4.6 (SD = 13.2) on a 52 point scale in the PAM-13 questionnaire between the Dutch (B) and German (C) groups (all using the dr. Bart app) with a power of 0.80 and an alpha of 0.05 (two-sided). The target sample will be able to detect a small to medium effect size (0.2–0.4) in primary outcomes (i.e. number of consultations in secondary health care and self-management behaviour) between groups.

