Second, (non)adherence to eHealth applications is considered a problem and as a consequence the effectiveness of these interventions possibly diminishes. In the dr. Bart app, a variety of elements (e.g. reminders) is incorporated to reinforce app engagement and in turn augment intervention effects [43, 50]. Moreover, the dr. Bart app is a standalone software application without human interaction, while it has been shown that blended options have more impact on health outcomes [50]. We assume, however, that the machine learning will provide tailored guidance and therefor better adherence to the treatment of OA.

Several strengths need to be underlined. The theoretical framework of the dr. Bart app is based on a solid rationale and the incorporated behavioural change techniques are chosen by specialists from different fields. In addition, all elements of the dr. Bart app are developed in co-creation with patient representatives and specialists. The design process of the dr. Bart app was based on an iterative design process resulting in a beta version which was pilot tested during a month in 21 people with OA. This is the first study that examines potential differences in use, usability and clinical outcomes of an e-self-management application for people with OA between the Netherlands and Germany.

In conclusion, this study will gain insight in the effectiveness of a standalone software application (dr. Bart app) equipped with machine learning techniques in the (conservative) treatment of people with knee and/or hip OA. Additionally, this study provides information regarding (cultural) differences in the (conservative) treatment of OA between the Netherlands and Germany.

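### The per-protocol contrast (adherent app users against all of usual care) is not a randomised comparison and cannot serve as a sensitivity check of the intention-to-treat result

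*Protocol article*

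**What the plan says.** Under (Planned) statistical analyses, the Protocol article states that "The primary analysis will be performed according to the intention-to-treat principle". It then adds a second analysis set for the Dutch trial: "a per-protocol analysis, including adherent participants of the dr. Bart group and the entire usual care group will serve as sensitivity analyses". The same section applies a two-sided 5% significance level to every analysis.

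The arms come from 1:1 randomisation: participants are "randomly allocated by the researcher to usual care (A) or dr. Bart (B) (allocation ratio 1:1"). On how adherence is observed, the section Adherence to the dr. Bart app says "Adherence to the dr. Bart app will be quantitatively measured in the back end of the app". Under Experimental intervention groups, the app opens only once the researcher has granted access. The Efficacy section describes the A versus B model as a mixed or count regression with treatment group, baseline value and a group-by-time term. It lists no predictors of adherence. The selection check that is planned compares study completers with non-completers, not adherent with non-adherent users.

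The Discussion takes non-adherence seriously: "non)adherence to eHealth applications is considered a problem and as a consequence the effectiveness of these interventions possibly diminishes". It then says that design elements and machine learning are meant to counter this. It gives no expected rate.

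**The concern.** Non-adherent participants are removed from one arm only. Their counterparts in usual care cannot be identified, because they have no app, so they all stay in. The groups compared are no longer those formed by randomisation.

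By the article's own behavioural model, acting on a goal depends on motivation and ability, and these vary between people. The Discussion also treats health care use as a proxy for self-management. It is therefore plausible that the traits that lead someone to use the app also affect consultations, activity and PAM-13.

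A sensitivity analysis should ask whether the same treatment effect survives a change of assumptions. This contrast estimates a different and possibly confounded quantity. Agreement with the intention-to-treat result would not confirm it, and disagreement would not undermine it. The practical risk is a null primary result beside a significant per-protocol result, read as evidence that the app works when used. The mirror image is also possible: a real benefit that seems to vanish.

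**Working it through.** **Inputs from the document (Sample size).** The design effect is stated as "a mean difference of 0.35 consultations between two independent groups was considered credible, with a standard deviation (SD) of 1.00". At 80% power and a two-sided 5% level the section arrives at 129 per arm, raised to 161 to allow for 20% attrition.

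**Reproducing the plan's figure.** n per arm = 2 × (1.960 + 0.842)² × (1.00 / 0.35)² = 128.1, rounded up to 129. Then 129 / 0.80 = 161.25, stated as 161. The design figures reproduce, and the point does not challenge them.

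**Inputs assumed, because the document gives none.** π is the share of arm B that is adherent. g is the expected outcome of non-adherent minus adherent people when the app has no effect, in SD units (SD 1.00, so also in consultations). r is the correlation between baseline and follow-up outcome, taken as 0.5 to 0.7.

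**Bias with no app effect.** Arm A has mean π·μ(adherent) + (1 − π)·μ(non-adherent). The retained part of arm B has mean μ(adherent). The size of the expected contrast is therefore (1 − π) × g. It favours the app if adherent people would have consulted less anyway (g > 0) and usual care if they would have consulted more (g < 0).

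**Unadjusted, π = 0.5, g = 0.3.**
- Bias = 0.5 × 0.3 = 0.15, which is 0.15 / 0.35 = 43% of the design effect.
- SE = √(1/129 + 1/64.5) = 0.1525.
- Bias / SE = 0.98. The rejection probability at two-sided 5% is 16.6% by the normal approximation and 16.5% by the noncentral t.

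**With the baseline value as covariate.** Suppose selection acts through the stable tendency shared by baseline and outcome. The adherent subset then differs by the same 0.15 at baseline. Adjustment removes r × 0.15 and shrinks the SE by √(1 − r²).
- r = 0.5: bias = 0.15 × 0.5 = 0.075; SE = 0.1525 × 0.866 = 0.132; rejection 8.8%.
- r = 0.7: bias = 0.15 × 0.3 = 0.045; SE = 0.1525 × 0.714 = 0.109; rejection 7.0%.

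Simulations of this case under a linear model gave bias of about 0.04 to 0.08 and rejection of 6% to 9%.

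**Range** (bias in SD, false-positive rate by the normal approximation):

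| π | g | Unadjusted | Adjusted, r = 0.5 | Adjusted, r = 0.7 |
|---|---|---|---|---|
| 0.5 | 0.3 | 0.150, 16.6% | 0.075, 8.8% | 0.045, 7.0% |
| 0.3 | 0.5 | 0.350, 48.0% | 0.175, 19.7% | 0.105, 12.6% |
| 0.7 | 0.2 | 0.060, 7.2% | 0.030, 5.7% | 0.018, 5.4% |
| 0.5 | 0.1 | 0.050, 6.2% | 0.025, 5.4% | 0.015, 5.2% |
| 0.9 | 0.3 | 0.030, 5.6% | 0.015, 5.2% | 0.009, 5.1% |
| any | 0 | 0, 5.0% | 0, 5.0% | 0, 5.0% |

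These are normal-theory figures on the design's own SD and sample size. The planned count models would change the decimals but not the mechanism.

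**The case against.** The strongest reply is that little depends on this analysis. Intention-to-treat is primary and the per-protocol set comes in addition. Keeping every control is a usual choice when controls have no app use by which to judge adherence. The adherence cut-off may sit in an analysis plan that is not shown. All of this stands, and the absence of a cut-off from the article is not held against it.

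The reply on size also stands in part. Unadjusted false-positive rates do not describe the plan, which adjusts for the baseline value, and adjustment halves the bias or better under the assumptions above. A reader might quote the 48% figure. It is a corner of an assumed grid (30% adherence, 0.5 SD gap, no adjustment) and falls to 13% to 20% once the baseline value is in the model.

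A reader might also infer that a favourable per-protocol result is the artefact to expect. The document does not support that. People with more complaints may use the app more and also consult more, and the contrast would then hide a benefit. Nor does the Discussion show that the excluded group will be large: it names a general eHealth problem and then states the hope of better adherence.

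Finally, a complier analysis is not assumption-free. Participants who complete no goal still receive daily notifications and can use the education and exercise libraries (Reminders, Education of OA, Physical activity and exercise library). An exposure defined by completed goals therefore strains the exclusion restriction. With no app use in controls, the estimate is essentially the intention-to-treat effect divided by the share exposed. It answers a further question and is not an independent check on the primary result.

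None of this rescues the label. The analysis set is stated outright, it selects on behaviour after randomisation in one arm only, and adjusting for the baseline value alone does not restore comparability.

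**Conclusion.** The point holds as a flaw in a supporting analysis that should be corrected. As written, the per-protocol contrast is non-randomised and cannot act as a sensitivity check. If adherence is related to prognosis it is biased by (1 − π) × g before adjustment, in a direction the document does not settle. In the worked case (50% adherence, 0.3 SD gap, no app effect), the bias is 0.15 SD with about 16.5% false positives unadjusted. With the planned baseline adjustment it is about 0.04 to 0.08 SD with 6% to 9%. The adherence rate, the gap and the baseline–outcome correlation are all assumptions, and the bias is zero if adherence and prognosis are unrelated. A reader might conclude that the trial's main result is at risk. It is not, because the intention-to-treat analysis keeps the randomised groups whatever the adherence.

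**What to change.** Make the supplementary analysis a complier average causal effect analysis that keeps all randomised Dutch participants, with allocation as instrument and logged app use as exposure. Two-stage least squares, or two-stage residual inclusion for counts, would serve. Because access must be released by the researcher, non-compliance is plausibly one-sided. Define exposure primarily as any use (for example app activated or first login), and show a goal-based threshold as a variation.

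If the adherent-versus-all-controls contrast is kept, label it exploratory, fix the adherence definition before outcome data are seen, and adjust for baseline predictors of adherence. Candidates are already collected in both Dutch arms: demographics, PAM-13, HOOS/KOOS, SQUASH, illness perception and treatment beliefs.

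**Cost.** No new data collection, provided that activation or first login can be extracted from the logs, and one extra analysis. The price is precision and an untestable assumption. The unadjusted intention-to-treat SE is √(2/129) = 0.125. At 50% exposure the complier SE is roughly 0.125 / 0.5 = 0.25, against 0.15 for the present contrast. The estimate also relies on the exclusion restriction, which should be stated beside the result.

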### Efficacy

Differences in the primary and secondary outcomes between the two arms of the RCT in the Netherlands (A vs. B) after 3 and 6 months will be assessed by either linear mixed models or Poisson regression, as appropriate, with a random intercept, including treatment group (i.e. usual care (A) or dr. Bart (B)), baseline value and interaction between treatment group and time as covariates. The primary outcome in the Netherlands will be reported as an incidence rate ratio in case of Poisson regression, or negative binomial regression, as appropriate.

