### Study parameters

#### Main study parameter

The main study parameter for the RCT in the Netherlands (arm A vs. B) is the number of self-reported consultations in secondary healthcare (i.e. orthopaedic surgeon, rheumatologist, physician assistant) due to OA in the knee and/or hip in the past 6 months, collected every 3 months. The primary endpoint in the Netherlands is the difference in mean consultations in secondary health care at 6 months between the usual care group (A) and the dr. Bart app group (B).

The primary endpoint for the comparison between the Dutch dr. Bart app group and the German dr. Bart app group (arm B vs. C) is self-management behaviour, as collected with the Patient Activation Measure (PAM-13) questionnaire [52, 53] at 6 months.

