### The Netherlands vs. Germany

Differences in means, at 3 and 6 months of follow-up, between the Dutch dr. Bart group (B) versus the German dr. Bart group (C) will be explored by mixed model repeated measures analyses with a random intercept, including country (i.e. the Netherlands or Germany), accompanying baseline value and interaction between country and time. Analyses will be corrected for relevant confounders; age, gender and BMI among others.

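### The A vs B model leaves out the hip/knee factor used to stratify randomisation; adding it is a small, free gain in precision

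*Protocol article*

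**What the plan says.** Under Randomization, allocation concealment and blinding, the protocol article allocates Dutch participants with "allocation ratio 1:1" in variable blocks, and the scheme "is stratified on the individual level by hip or knee OA".

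The Efficacy section covers both follow-up visits and gives the A vs B covariates as a list: "including treatment group (i.e. usual care (A) or dr. Bart (B)), baseline value and interaction between treatment group and time as covariates". Depending on the outcome, the model is a linear mixed or a Poisson model. Hip/knee is not listed. Time appears only inside the interaction, and its coding is not stated.

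Under Main study parameter: "The primary endpoint in the Netherlands is the difference in mean consultations in secondary health care at 6 months".

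The B vs C model, under The Netherlands vs. Germany, follows the same pattern, "including country (i.e. the Netherlands or Germany), accompanying baseline value and interaction between country and time". It then adds adjustment for age, gender and BMI in a list that is left open.

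**The concern.** Stratified randomisation balances the arms on the affected joint, so the true sampling variance of the treatment difference no longer contains the between-joint part of the outcome variance. A model without the joint leaves that part in the residual and reports a standard error that is too large. The benefit of stratifying is then only partly realised: intervals are wider than needed and some power is lost.

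Joint could plausibly be prognostic for some outcomes here. Pain, function and quality of life are measured with HOOS or KOOS depending on the affected joint, so those analyses pool two instruments split along this factor. The article gives no figure for how strongly joint predicts any outcome.

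The same model sentence names a group-by-time interaction without a time main effect. At issue there is whether the 6-month contrast, which is the primary endpoint, would be estimated as intended.

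**Working it through.** **Inputs from the Sample size section.** Difference 0.35 consultations, SD 1.00, two-sided alpha 0.05, power 0.80, 129 per arm, 161 after 20% loss.

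**The plan's own figure.** n = 2 × (1.960 + 0.842)² × 1.00² / 0.35² = 128.2, rounded up to 129, as stated (the exact t calculation gives 130). 129 / 0.80 = 161.25, stated as 161. Power at 129 per arm is 80.3%.

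**Leaving out the stratum.** Let R² be the share of outcome variance explained by joint beyond the baseline value. The documents do not give it, so 0.01 to 0.10 is an assumed range. The SD of 1.00 is taken as the residual SD before joint is added, and stratification is taken to balance joint across arms. Put s = √(1 − R²).

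- Standard error reported without adjustment: √(2/129) = 0.1245. Actual standard error: s × 0.1245.
- Actual alpha without adjustment: 2 × [1 − Φ(1.960 / s)].
- Power without adjustment: Φ[(0.35/0.1245 − 1.960) / s].
- Power with adjustment: Φ[0.35/(s × 0.1245) − 1.960].

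| Assumed R² | Actual alpha, unadjusted | Power, unadjusted | Power, adjusted | Gain (points) | n per arm for 80%, adjusted |
|---|---|---|---|---|---|
| 0.01 | 0.0489 | 0.8038 | 0.8065 | 0.3 | 127 |
| 0.02 | 0.0477 | 0.8050 | 0.8104 | 0.5 | 126 |
| 0.05 | 0.0443 | 0.8087 | 0.8223 | 1.4 | 122 |
| 0.10 | 0.0388 | 0.8151 | 0.8421 | 2.7 | 116 |

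The comparator matters. Under stratified allocation the unadjusted test already has slightly more than 80.3% power, so the gain at R² = 0.10 is 84.2 − 81.5 = 2.7 points, not 84.2 − 80.3 = 3.9.

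**Time term.** Two readings of the listed terms were compared.

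- *Categorical time, interaction fitted for all arm-by-visit cells.* Group plus group-by-time spans the four cell means, so the fit equals that of the full model.
- *Numeric or single-dummy product with no time main effect.* The usual care mean is held equal at 3 and 6 months. The 6-month contrast becomes B6 − (A3 + A6)/2, which is off by half the control-arm change.

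A check used 150 simulated data sets with a linear model, 129 per arm, no app effect, and assumed values of 0.5 for within-person correlation and 0.20 for the common change from 3 to 6 months. The mean 6-month contrast was 0.006 for the full model, 0.006 for the categorical-cell model and 0.105 for the product-only model (expected 0.20/2 = 0.10; Monte Carlo standard error about 0.008). With no control-arm change the bias is zero.

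**The case against.** **It is a condensed article.** The full protocol or analysis plan may name the stratum. That would answer a complaint about silence, but the article is not silent: it lists the A vs B covariates, and the list does not match the randomisation it describes. For B vs C it does name extra covariates.

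**The effect is small and in the safe direction.** This stands. In the linear model the omission causes neither bias nor an excess of false positives, and the size depends on an R² that nobody has reported. The figures do not carry over directly to the Poisson or negative binomial option, for which no calculation was made.

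**The covariate is not fully defined.** This also stands. Eligibility allows knee and/or hip complaints, while the stratum is hip or knee, so participants with both need a stated rule.

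**Stronger readings that do not hold.** A reader might infer that the missing time main effect biases the primary 6-month result. The text does not support that. It does not say how time is coded, categorical coding gives the same fit as the full model, and naming an interaction in a condensed article commonly implies its main effects. A reader might also extend the stratum point to B vs C. That comparison is not randomised, is described as exploratory and has an open confounder list, so affected joint is not excluded.

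**Conclusion.** The A vs B model omits the factor on which the Dutch randomisation is stratified. If joint is prognostic beyond baseline, the consequence in the linear model is conservative inference: actual alpha of about 0.049 to 0.039 and a loss of about 0.3 to 2.7 power points, for an assumed R² of 0.01 to 0.10 at 129 per arm. If joint is not prognostic, nothing is lost. There is no bias either way.

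The time term is an ambiguity to remove, not a demonstrated error. Bias would require a numeric or single-dummy interaction, no implied main effect and a real control-arm change between 3 and 6 months; the documents establish none of these.

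This is a free improvement, not a threat to the trial's validity.

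**What to change.** Restate the model for every A vs B outcome as: arm, time (categorical: 3 and 6 months), arm-by-time, baseline value, hip/knee stratum and a random intercept, with the 6-month arm contrast as primary. Code the stratum exactly as it was used at randomisation, and say in which stratum participants with both joints affected were placed. Writing time out as a main effect in the B vs C model would make the two statements consistent.

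The cost is one sentence. The stratum is already recorded for randomisation, and the sample size need not change. The only preparatory work is to document the rule for participants with both joints affected.
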